## Abstract

**Background:**

In treating patients with cervical ossification of the posterior longitudinal ligament (COPLL), a novel surgery technique - anterior controllable antedisplacement and fusion (ACAF) suggested promising clinical benefits in recent exploratory studies.

**Methods:**

This is a multicentre, randomized, open-label, parallel-group, active controlled trial that will compare the clinical benefits of ACAF versus conventional posterior laminoplasty (LAMP) in severe COPLL patients. A total of 164 patients will be enrolled and randomized in a 1:1 ratio to either ACAF or LAMP group. The primary efficacy measure is cervical- Japanese Orthopaedic Association (C-JOA) recovery rate at 12 months post operation, which is to be derived by Hirabayashi’s method from JOA data (range, 0 [worst] to 17 [normal condition]). Other important secondary efficacy endpoints include visual analogue scale (VAS) pain score (range, 0 [no pain] to 10 [most severe]), 10-item neck disability index (NDI, a total range of 0 to 50 points, the highest index the worst) and 6-level Nurick disability grade (range, 0 [mild] to 5 [severe]). Safety endpoints including adverse events, perioperative complications, and adverse events of special interest will also be assessed in this study. Full analysis set for baseline and efficacy data analyses according to the intention-to-treat principle will be established as the primary analysis population. Analysis of covariance (ANCOVA) will be used to analyze the C-JOA recovery rate, with random stratification factors (if appropriate) and the treatment group as fixed factors, and the baseline level of C-JOA score as covariate.

**Discussion:**

This study is designed to demonstrate the clinical benefits of ACAF as compared to conventional LAMP in COPLL patients. It will provide clinical evidence that the novel surgery technique – ACAF might be more favorable in treating patients with severe cervical ossification of the posterior longitudinal ligament. (Words: 290).

**Trial registration:**

ClinicalTrials.gov number, NCT04968028.

## Background

Ossification of the posterior longitudinal ligament (OPLL) is a pathologic process of lamellar bone deposition at the site of the posterior longitudinal ligament (PLL) [1]. And it often occurs in the cervical spine, which was first noticed in the Japanese patients and reported more commonly in Asian countries than North America, with a prevalence rate of 2 to 4% in Japan [2], 3.1% in China [3], 5.1% in India [4] and 2.5% in USA [5], respectively. As one kind of chronic and multifactorial disease, it usually causes spinal cord compression over time and lead to a reduced range of cervical motion [1],, and further serious neural injury like axial neck pain, diminished sensation, motor weakness, and changes in balance or gait stability, or more severely, incontinence, paralysis, severe respiratory failure and even death [1, 4–6].

Non-operative management can be often undertaken for asymptomatic patients without severe cord compression or myelomalacia on radiographic scans [6–9]. However, for patients with neurologic symptoms such as myelopathy or radiculopathy or evidence of spinal cord compression, surgical intervention is required and also the only effective treatment options to date [6–10]. Mainstream surgical approaches available currently are those utilizing anterior (ACCF, anterior cervical corpectomy and fusion), posterior (LAMP, laminoplasty; LF, laminectomy and fusion), or combined anteroposterior strategy, each with different levels of risks and benefits [1, 11]. Anterior approaches are technically more demanding and associated with higher rates of spinal cord injury, cerebrospinal fluid leak, dysphagia, dysarhtria, hoarseness but offer direct decompression for ventral OPLL pathology. Although posterior own higher safety, associated with higher rates of C5 palsy, axial pain, and may allow for ossification progression that lead to recurrence of neurological deterioration [11, 12]. Even so, high level of clinical evidence is still inconclusive so far [12], therefore, surgeons and patients have to subjectively decide on surgery strategy after individualizing the potential benefits of surgical decompression against the potential medical and surgical complications [1, 12].

To make full use of the estimated advantages of anterior and posterior approaches and maximally avoid disadvantages, we have designed a novel surgery technique - anterior controllable antidisplacement and fusion (ACAF) strategy in a hope to achieve anterior direct decompression without removing the OPLL [13–15]. Our preliminary results in the recent exploratory studies [13, 14], along with those found in a Korean case series report (*N* = 24) [16] suggested that ACAF technique is an effective and safe option for anterior decompression surgery in severe OPLL patients. Given a worldwide paucity of level-I evidence comparing surgical approaches to OPLL [11] and potential expert consensus or clinical practice guideline to come out, we designed this adequate and well-controlled investigation across multiple study sites in China. Here we present its rationale, methodology and analysis plan on how to compare the clinical effectiveness of ACAF technique against LAMP among severe COPLL patients. The randomized controlled trial aims to provide clinical evidence that ACAF might be more favorable in treating severe COPLL patients.

## Methods and design

### Study design

The STAR study (ClinicalTrials.gov number, NCT04968028) is a multicentre, randomized, open-label, parallel-group, active controlled trial that aims to demonstrate more favorable clinical benefits of ACAF as compared to conventional LAMP in severe COPLL patients. It will be conducted following the Consolidated Standards of Reporting Trials (CONSORT) statement (http://www.consort-statement.org/). Approximately twelve clinical centres in China will participate in this study. A brief flowchart of this study is provided in Fig. 1.

**Fig. 1 Fig1:**
[figure not shown]
Study flow chart. Abbreviations: ACAF, anterior controllable antedisplacement and fusion; C-JOA, cervical Japanese Orthopaedic Association; LAMP, posterior laminoplasty; NDI, neck disability index; VAS, visual analogue scale

### Study patients

A total of 164 eligible patients will be enrolled and randomized after screening at the study sites. The following are the inclusion criteria:
The patient’s age is 18–70 years old, regardless of gender;The patient was diagnosed as severe ossification of the posterior longitudinal ligament (X-ray or computed tomography [CT] showed ossification of the posterior longitudinal ligament). The imaging findings showed occupied ratio ≥ 60% or involved three or more segments.Symptoms of spinal cord and nerve root compression, or accompanied by spinal cord compression symptoms such as dysfunction of urination and defecation, conservative treatment was ineffective or aggravated gradually;The participant (or his legal guardian) can sign the informed consent.The exclusion criteria are as follows:Congenital malformations (including but not limited to occipitocervical malformations, congenital cervical fusion, cervical related neurovascular malformations), ossification of cervical ligamentum flavum, cervical trauma, cervical cancer, cervical tuberculosis and other inflammatory diseases;Patients with other spinal diseases such as thoracolumbar vertebrae that affect clinical symptoms; Patients with motor neuron diseases such as amyotrophic lateral sclerosis and other nervous system diseases;The symptoms were aggravated due to recent trauma;Patients who participated in other clinical trials in recent 3 months;The participant (or his legal guardian) with mental illness and cognitive impairment cannot give full informed consent;Those who are in poor health and cannot tolerate surgery; the patients were not suitable for surgical treatment after preoperative examination.

### Recruitment and randomization process

Before enrollment, there will be one pretreatment screening visit at study site office, during which each participant will be assigned a unique identification number.

Once considered eligible for entry, these COPLL patients will be randomly assigned to one of two study treatment groups, e.g. either ACAF or LAMP surgery in a 1:1 ratio. A stratified randomization using minimization technique [17, 18] will be carried out, stratified by study site, occupation ratio (< 60% versus ≥60%), K-line status (negative versus positive) and count of vertebrae involved (< 3 versus ≥3). Random assignment is generated by an independent statistician and implemented via central randomization mobile phone APP (Shanghai KNOWLANDS MedPharm Consulting Co., Ltd.). In order to avoid potential selection bias, the randomization sequence is concealed in APP from both clinical staff and patients until assignment. Hence, neither any investigators nor patients can influence which treatment group the study patients are assigned to.

### Description of the interventions

The enrolled subjects will be randomized to undergo the novel ACAF or conventional LAMP surgery. In order to minimize the potential bias of the trial data, all patients would be operated on by senior spine surgeons from spine surgery team at each site who are highly experienced in performing the two trial interventions. All patients in the study will accept the same surgical devices. All the consumables used in the operation are from the same manufacturer, and the operations will be carried out in strict accordance with the unified standard.

#### ACAF group

The surgical steps of ACAF were as follows: (1) a standard right-side Smith–Robinson approach was performed to expose the cervical spine, and intraoperative fluoroscopy was used to confirmed surgical levels. (2) The involved disc tissue was completely removed. The posterior longitudinal ligament was only cut down at the levels cephalic and caudal to OPLL, and the osteophytes at the anterior and posterior borders of vertebrae were appropriately removed for placing cages at the middle disc levels. (3) The anterior portion of the middle vertebral bodies with OPLL was appropriately removed according to the thickness of ossification. Suitable cages filled with autologous bone fragments were placed into each intervertebral space. (4) On the left side of the vertebra, high-speed burr and Kerrison rongeur were used to create a 2-mm-wide groove on the lateral side of vertebral body, approximately at the medial border of the transverse foramina. After that, an appropriate curved plated was fixed to the caudal and cephal ad vertebrae. On the middle vertebrae, screws were inserted halfway for temporary fixation. (5) On the right side of the vertebrae, as had performed on the left side, a similar groove was also created, and the vertebrae with OPLL were completely isolated. (6) Finally, the loose screws on the middle vertebrae were tightened to achieve a gradual evaluation of the vertebrae with OPLL, resulting in decompression of the spinal cord (Figs. 2A – 2E). The SKYLINE anterior cervical plate system with PEEK cage (Depuy Synthes Spine, Inc., Raynham, MA) was used in all patients. After surgery, all patients were immobilized in a Philadelphia collar for 6 to 8 weeks.

**Fig. 2 Fig2:**
[figure not shown]
Schematic diagram of ACAF technique with steps A through E: (**A**) Expose and confirm surgical levels; (**B**) Remove discs, decompress at the levels cephalic and caudal to OPLL and remove the anterior portion of the middle vertebral bodies with OPLL; (**C**) Place interbody cages and create a groove on the left side, and fix anterior plate; (**D**) Create a groove on the right side, and isolate the vertebrae with OPLL and (**E**) Evaluate the vertebrae with OPLL. Sagittal (left) and transverse (right) sectional images of the cervical spine. Abbreviations: ACAF, anterior controllable antedisplacement and fusion; OPLL, ossification of the posterior longitudinal ligament

#### LAMP group

The surgical procedure of laminoplasty will be done as described in the literature using the ARCH miniplate fixation system (Depuy Synthes Spine, Inc., Raynham, MA). After surgery, all patients will be immobilized in a Philadelphia collar for 3 to 4 weeks.

As for the other treatments other than study surgery, including the perioperative treatment, study patients in the two groups both will follow Chinese Experts Consensus (2018) [19].

### Study visits

Six study visits per subject are scheduled in the study as follows: pre-treatment visit (Day − 28 to Day − 1), perioperative visit (Day 1 until discharge) and follow-up visit at month 3 ± 1 week, month 6 ± 1 week, month 12 ± 2 week and month 24 ± 4 week (Month 3, 6, 12 and 24 post treatment). These visits will be made at study site office or patient ward as appropriate. At scheduled visits, data relating to demography, vital sign, operating time, estimated blood loss during operation period, length of stay at hospital in days, and perioperative complications, cervical Japanese Orthopaedic Association (C-JOA) score and visual analogue scale (VAS) pain score, Neck Disability Index (NDI), Nurick score, concomitant medication / treatment, new adverse events, radiographic data, revision surgery etc. will be collected. See Fig. 1 for more details.

In case severe adverse events occur, the subject can drop out at any time during the study.

### Outcome measures

#### Primary efficacy outcome

The primary efficacy endpoint is the C-JOA recovery rate at 12 months post operation, which is to be derived by Hirabayashi’s method [20] from original C-JOA scores. A set of C-JOA score per subject visit involves four aspects: upper limb motor function (range, 0 to 4 points), lower limb motor function (range, 0 to 4 points), sensory function (range, 0 to 6 points), and bladder function (range, 0 to 3 points). The total C-JOA score ranged from 0 (worst) to 17 (normal condition), with a lower score indicating more significant dysfunction. The recovery rate of C-JOA is calculated by the following Hirabayashi’s formula [20]:
$$ \mathrm{C}-\mathrm{JOA}\mathrm{recovery}\ \mathrm{rate}=\frac{\mathrm{Post}\ \mathrm{minus}\ \mathrm{Preoperative}\ \mathrm{C}-\mathrm{JOA}\ \mathrm{score}}{17\ \mathrm{minus}\ \mathrm{Preoperative}\ \mathrm{C}-\mathrm{JOA}\ \mathrm{score}}\times 100\% $$

#### Secondary outcomes

The secondary efficacy outcomes in this study included VAS pain score (range, 0 [no pain] to 10 [most severe]) [21], 10-item NDI (a total range of 0 to 50 points, the highest index the worst) [22] and 6-level Nurick disability grade (range, 0 [mild] to 5 [severe]) [23].

Safety endpoints.

The safety endpoints include any adverse events (AEs), perioperative complications, and adverse events of special interest. The AEs profile of both treatments will be evaluated by examining the incidence of AEs according to the National Cancer Institute Common Terminology Criteria for Adverse Events (NCI CTCAE, Version5.0) [24].

### Sample size calculation

We used SAS® software, V.9.4 (SAS Institute, North Carolina, USA) to estimate sample size. According to the principle of efficacy superiority design, the significance level α was set as 0.05 at two-sided. The primary efficacy endpoint of this study is the recovery rate of C-JOA at the 12th month of follow-up post operation. Assume that in severe COPLL patient population, the mean recovery rate of C-JOA in the ACAF group and the LAMP group at 12 months after operation is 63 and 51% (a mean difference of 12%), respectively, and the common standard deviation is 20%. When the two groups are randomly assigned 148 subjects in a 1:1 ratio, the statistical power can reach as high as 95%. If the subject dropout rate is 10% or less, 164 eligible subjects with severe COPLL should be randomly enrolled.

### Statistical analysis

The study includes three analysis populations per analysis plan. For the baseline and efficacy data, we will use full analysis set (FAS), which includes all subjects who were randomized into the study groups and received the study operation scheme. According to the principle of intention to treat, subjects in FAS would be analyzed using their randomly assigned group, regardless of the actual surgical treatment received. Per-protocol population, e.g. a subset of FAS will be established further for subjects with no major protocol deviation(s), which will be reviewed and determined by the sponsor before the study database is locked. Safety set (SS) is defined to include all subjects who have received the treatment of the study-specified operation (regardless of whether they participate in the randomized assignment or not) and will be the primary analysis population for safety data. The subjects in SS will be grouped according to the actual surgical treatment received.

In this study, a two-sided *p*-value of 0.05 or less (equivalently one-sided p-value of 0.025) will be considered to indicate significance for any statistical tests, unless otherwise specified in the interim analysis section. Software R, V.4.0.4 [25] and SAS®, V.9.4 will be used for statistical analysis. Such data as demographics, baseline characteristics, surgery operation, radiographic data and safety will be summarized according to treatment group.

The primary endpoint of this study is the C-JOA recovery rate at 12 months post operation. It will be analyzed with the use of analysis of covariance (ANCOVA), with random stratification factors (if appropriate) and the treatment group as fixed factors, and the baseline level of C-JOA score as covariate. The least squares mean (LSM), the difference from the control group and the confidence interval (CI) of each treatment group will also provided for statistical analysis.

In addition, a mixed model repeated measures (MMRM) will be used as supportive analysis when appropriate. MMRM analysis includes treatment group, time and time treatment group interaction as fixed effects, baseline level as covariate, and patients as random effects. When there are missing data, multiple imputation method will be applied as the primary analysis; those results from the last observation carry forward method (LOCF) and the as-observed data analysis will play roles as sensitivity analyses. If the data distribution does not meet the statistical hypothesis of ANCOVA, a set of rank-based analysis will be the primary one. The LSM, the difference from the control group and the CI of each treatment group will be also provided for statistical analysis. For MMRM and ANCOVA, the two-sided *p*-values will be provided when compared with the control group.

To investigate the consistency of the trial conclusions among different subpopulations, the subgroup analysis with regards to the primary efficacy endpoint will include but not limited to the following baseline factors: gender; age group; duration of complaining symptoms; diabetes status; smoking status; count of vertebrae segments involved; type of COPLL; K-line status; occupation ratio; C-JOA score; Nurick grade and status of hypersignal of spinal cord. The occupation ratio (OR) is defined as the biggest ratio of COPLL thickness to anteroposterior diameter of the bony spinal canal on the axial computed tomography image. A forest plot will be also provided as a useful display of estimated treatment effects across subgroups.

For VAS pain score and NDI index as continuous variables, the analysis method of between-group comparison is similar to those used for the primary endpoint. For cervical Nurick grades as an ordinal variable, the common odds ratio will be estimated by using ordinal logistic regression analysis (proportional odds model) to reflect the shift of full distribution of each grade between the two groups 12 months after operation. The adjusted and unadjusted common odds ratio and its 95% CIs will be calculated. When using the model to adjust prognostic factors, the important prognostic factors mainly include random stratification factor as appropriate, gender, age and baseline Nurick score, which will be clearly specified in the statistical analysis plan before the database lock.

For purposes indicative of statistical significance, we will use the Cochran Mantel Haenszel (CMH) method according to random stratification factors as appropriate to test the statistical hypothesis for important categorical adverse events. The incidences in each group and 95% CIs of incidence difference between the two groups will be calculated by Newcombe method [26]. Similar statistical analysis will also be conducted for each single adverse event of special interest, or Fisher’s exact test will be used for comparison between groups when applicable.

Radiographic data based on central review as their primary analyses will be compared between groups. When appropriate, we will also conduct exploratory analysis on the relationship between these imaging data and clinical outcomes, with an effort to predict the long-term clinical outcomes and complications with the use of preoperative and recent postoperative imaging data as well as other subject-level baseline characteristics. The statistical methods used for these exploratory analyses will be depicted in more details in the statistical analysis plan as appropriate.

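### The full analysis set is a modified intention-to-treat set that omits randomised patients without the study operation, and no listed population contains everyone randomised

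*Protocol article*

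**What the plan says.** The Statistical analysis section names three populations. The FAS, used for baseline and efficacy data, is the one "which includes all subjects who were randomized into the study groups and received the study operation scheme". The article then adds that "subjects in FAS would be analyzed using their randomly assigned group, regardless of the actual surgical treatment received". The per-protocol set is a subset of the FAS, and the safety set requires that a study operation was performed.

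The abstract (Methods) gives the FAS its role and its label: "Full analysis set for baseline and efficacy data analyses according to the intention-to-treat principle will be established as the primary analysis population".

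Two design features bear on the point. Study design describes a "multicentre, randomized, open-label, parallel-group, active controlled trial". Under Recruitment and randomization process, "the randomization sequence is concealed in APP from both clinical staff and patients until assignment", so concealment ends at assignment, and surgery comes after it.

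The primary endpoint (Primary efficacy outcome) is timed at 12 months after the operation. Missing data are handled mainly by multiple imputation. The article does not say that imputation reaches anyone outside the FAS.

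**The concern.** Having the operation is an event after randomisation, yet it decides who enters the primary efficacy set. The intention-to-treat sentence governs only how patients already in the FAS are grouped. It brings back nobody who was left out at entry.

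In an open-label surgical trial, patient and surgeon can know the arm before the event that determines membership. The article's Background describes different risk profiles for anterior and posterior surgery, and ACAF is the new technique. Withdrawal before surgery could therefore be more common in one arm and could be related to expected outcome. If so, the groups compared at 12 months are no longer the groups that were randomised, and the 12-month C-JOA difference is biased in a direction that cannot be known in advance.

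No other listed population would reveal this. Baseline data are also reported on the FAS, so the baseline table would not show who had been removed.

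**Working it through.** **1. Does any listed set hold all randomised patients?**

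| Set | Entry condition | Contains randomised, unoperated patients? |
|---|---|---|
| FAS | randomised and received the study operation | no |
| Per-protocol | subset of the FAS | no |
| Safety | received a study operation | no |

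The article states that "The study includes three analysis populations per analysis plan", and none of the three contains these patients.

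**2. Who is affected?** A patient assigned to ACAF who has LAMP, or the reverse, has had a study operation and is analysed as assigned. A patient with no operation is excluded. A patient who has some other procedure is not clearly covered either way by the wording.

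**3. The plan's own sample size.** Inputs from Sample size calculation: means 63% and 51% (difference 12 points), SD 20, two-sided alpha 0.05, power 95%, 148 evaluable, 10% dropout, 164 randomised.

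- Normal approximation: n per arm = 2 × (1.960 + 1.645)² × 20² / 12² = 72.2, so 73. The t-test solution is 73.2, so 74 per arm, which is 148.
- Power with 74 per arm: 95.4% (normal), 95.2% (t-test).
- Dropout: 148 / 0.9 = 164.4, against 164 stated.

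The stated figures reproduce, and none is disputed here.

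**4. Size of a possible bias.** Assumptions, because the article gives no rates:

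- One arm only loses a share f of its 82 randomised patients.
- The patients lost would have scored g points worse than those retained.
- There is no true difference between the arms.

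Then:

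- bias = f × g
- standard error = 20 × √(1/82 + 1/(82(1 − f)))
- two-sided type I error = Φ(−1.96 + bias/SE) + Φ(−1.96 − bias/SE)

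| f | g (points) | Bias (points) | Share of 12 points | Type I error |
|---|---|---|---|---|
| 2% | 20 | 0.4 | 3% | 5.2% |
| 5% | 10 | 0.5 | 4% | 5.3% |
| 5% | 20 | 1.0 | 8% | 6.2% |
| 10% | 10 | 1.0 | 8% | 6.1% |
| 10% | 20 | 2.0 | 17% | 9.6% |

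Example for f = 5%, g = 20: SE = 20 × √(1/82 + 1/77.9) = 3.16; 1.0 / 3.16 = 0.316; type I error = 0.0501 + 0.0114 = 0.0615.

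If both arms lose similar shares with similar gaps, the two biases largely cancel. If g = 0, there is no bias.

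**5. Power cost of keeping everyone.** Assume a share f of each arm is unoperated, is kept in the analysis and shows no between-arm difference. The difference is then diluted to 12(1 − f).

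| f | Diluted difference | Power, 82 per arm | Power, 74 per arm |
|---|---|---|---|
| 2% | 11.76 | 96.4% | 94.7% |
| 5% | 11.40 | 95.4% | 93.4% |
| 10% | 10.80 | 93.3% | 90.7% |

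**The case against.** A sponsor could fairly answer as follows.

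- **Crossovers are protected.** A reader might infer that anyone who declines the allocated operation disappears from the primary analysis. The text does not support that: a patient who changes from one study operation to the other stays in the assigned arm. This stands, and it confines the point to randomised patients who do not receive the study operation.
- **Few patients should go unoperated.** The eligibility criteria exclude those unable to tolerate surgery or found unsuitable on preoperative examination, and eligibility is settled before randomisation. Entry requires compressive symptoms that are worsening or have not responded to conservative treatment. The pre-treatment visit falls within 28 days of surgery. This stands as a reason to expect small numbers, but it does not make them zero.
- **Differential loss is not shown.** A reader might infer that reasons for non-operation will differ between the arms. The article shows only that they may: it gives no rates or reasons by arm.
- **The larger scenarios are adverse.** A 10% loss in one arm uses that arm's full all-cause dropout allowance before surgery, with nothing offsetting it in the other arm. This stands, and the 2% case belongs beside it.
- **Redefining the set is not enough.** The endpoint is timed from the operation, so it has no date in an unoperated patient. Imputing from operated patients would give operated-like values and an estimate close to the present one. This stands, and it shapes the fix.

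The reply that the definition can be left to an unseen analysis plan does not stand. The article itself fixes both the definition and the intention-to-treat label.

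**Conclusion.** The point holds as a mismatch between label and definition that carries a risk of bias. The primary efficacy set is modified intention to treat, is described as following intention to treat, and is not backed by any all-randomised population.

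Bias is possible because allocation is known before the event that decides membership, but the article does not demonstrate it. Its size rests on two unknowns: how many randomised patients go unoperated in each arm, and how their outcomes would differ. With a 20-point gap and loss in one arm only, it runs from 0.4 points at 2% to 2.0 points at 10%, with type I error from about 5.2% to 9.6%. It is probably small if few go unoperated, and near zero if losses are balanced or unrelated to prognosis.

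A reader might go further and call the primary comparison invalid. The documents do not support that, given the protection of crossovers and the screening for surgical fitness before randomisation. This should be fixed, but it does not undermine the design.

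**What to change.** 1. Define the primary efficacy set as all randomised patients, analysed as randomised, whether or not the study operation took place.
2. For patients not operated on, schedule and collect C-JOA at 12 months from randomisation. Use multiple imputation only where that score is still missing.
3. Keep the randomised-and-operated set as a sensitivity analysis and label it modified intention to treat.
4. Report the number of unoperated patients and the reasons, by arm.

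The change should be made before any unblinded comparison. It should also be made early enough to follow these patients, because outcomes never collected cannot be recovered later.

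The cost is a revised definition, a visit anchor and follow-up of what may be only a few extra patients. The time origin will differ between operated and unoperated patients, and this should be stated openly. The target of 164 does not change. Dilution is slight: if 5% of each arm is unoperated and shows no between-arm difference, power is about 95.4% with 82 per arm, or 93.4% with 74.
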